**C. First Elevated BP in last 24 months at healthcare maintenance or non-acute care visit**

1. Date of visit with first elevated BP noted (MM/DD/YYYY): \_\_/\_\_/\_\_\_\_ [THESE DATA ARE ENTERED INTO REDCAP BUT NOT GIVEN TO RESEARCH TEAM]

- 1a. Height at **this visit with an elevated blood pressure** \_\_\_\_\_ (centimeters) ☐ Not done at this visit  
1b. Weight at **this visit with an elevated blood pressure** \_\_\_\_\_ (kilograms) ☐ Not done at this visit  
2. Initial Systolic Blood Pressure: \_\_\_\_\_ Systolic Percentile: \_\_\_\_\_ ☐ Percentile unknown  
3. Initial Diastolic Blood Pressure: \_\_\_\_\_ Diastolic Percentile: \_\_\_\_\_ ☐ Percentile unknown  
4. Blood pressure measured by: ☐ Automated (Oscillometry) [Go to 4a] ☐ Manual (Auscultation) [Go to 4d]  
4a. If Automated: was BP remeasured twice with automated device? ☐ Yes [Go to 4a.i] ☐ No [Go to 4c]  
4a.i. If Yes, what were 2 additional results: Systolic Blood Pressure #2: \_\_\_\_\_  
Diastolic Blood Pressure #2: \_\_\_\_\_

Systolic Blood Pressure #3: \_\_\_\_\_

Diastolic Blood Pressure #3: \_\_\_\_\_

[Go to 4b]

4b. Was average of 2 repeat automated BP still elevated ( $\geq$  90th percentile for patient's height, weight and sex, or  $\geq$ 120/80)?

☐ Yes [Go to 4d] ☐ No [STOP COMPLETING FORM]

4c. Was repeat automated BP measured only one more time? (i.e. it was not remeasured twice and averaged)

☐ Yes and it was normal [STOP COMPLETING FORM]

☐ Yes and it was still elevated ( $\geq$  90th percentile for patient's height, weight and sex, or  $\geq$ 120/80) [Go to 4d]

☐ No, BP Not re-measured [Go to 5]

4d. If first Manual was abnormal, or repeat automated BPs still elevated: was BP remeasured twice with manual?

☐ Yes [Go to 4d.i] ☐ No [Go to 4e]

4d.i. If Yes, what were 2 additional results: Systolic Blood Pressure #2: \_\_\_\_\_

Diastolic Blood Pressure #2: \_\_\_\_\_

Systolic Blood Pressure #3: \_\_\_\_\_

Diastolic Blood Pressure #3: \_\_\_\_\_

4d.ii. Was average of 2 Manual BPs still elevated ( $\geq$  90th percentile for patient's height, weight and sex, or  $\geq$ 120/80)?

☐ Yes [Go to 5] ☐ No [STOP COMPLETING FORM]

4e. Was repeat Manual BP measured only one more time? (i.e. it was not remeasured twice and averaged)

☐ Yes and it was normal [STOP COMPLETING FORM]

☐ Yes and it was still elevated ( $\geq$  90th percentile for patient's height, weight and sex, or  $\geq$ 120/80) [Go to 5]

☐ No, BP Not re-measured [Go to 5]

5. Did provider document that the following were discussed with patient and/or family:

5a. Weight counseling ☐ Yes ☐ No ☐ N/A patient has normal BMI

5b. Nutrition counseling ☐ Yes ☐ No

5c. Lifestyle modifications ☐ Yes ☐ No

6. Did the patient have BP in Stage II Hypertension range ( $\geq$ 95th+12mm to <95th+30mm; or  $\geq$ 140/90 to <180/120)?

☐ Yes [Go to 6a] ☐ No [Go to 7]

6a. If patient had BP in Stage II Hypertension range ( $\geq$ 95th+12mm or  $\geq$ 140/90) were both upper extremities and 1 lower extremity blood pressure taken and documented?

☐ Yes [Go to 6b] ☐ No [Go to 7]

6b. If yes, were they normal? ☐ Yes [Go to 7] ☐ No [Go to 6c]

6c. If abnormal, was a referral request to a subspecialist made? ☐ Yes [Go to 6d] ☐ No [Go to 7]

\*Did someone in the clinic tell the patient/family they needed to see a subspecialist and complete referral paperwork?

6d. If a subspecialist referral was made, which specialist? (Check all that apply):

☐ Nephrologist ☐ Cardiologist ☐ Other: \_\_\_\_\_

6e. ☐ N/A: Patient never attended subspecialist visit [Go to 7]

[IF N/A NOT CHECKED] Date first subspecialist visit completed (MM/DD/YYYY): \_\_/\_\_/\_\_\_\_ [THESE DATA ARE ENTERED INTO REDCAP BUT NOT GIVEN TO RESEARCH TEAM]

\*Not date referral request made, but date patient actually saw subspecialist

6f. Date information on the patient was received from subspecialist back to the pediatrician:

(MM/DD/YYYY): \_\_/\_\_/\_\_\_\_ [THESE DATA ARE ENTERED INTO REDCAP BUT NOT GIVEN TO RESEARCH TEAM]

\*If same electronic health record, enter date note was signed by the subspecialist

7. Was a follow-up appointment recommended or made for the patient with the primary care practice?

☐ Yes [Go to 7a] ☐ No [Go to Section D]

7a. If yes, what date was the follow-up appointment scheduled for? (MM/DD/YYYY): \_\_/\_\_/\_\_\_\_ [THESE DATA ARE ENTERED INTO REDCAP BUT NOT GIVEN TO RESEARCH TEAM]

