| Primary Outcome Measure    | Number of patients without all correct diagnostic and management decisions (Figure 4) per 100 patients with measured elevated BP                                                                                                                                                                                                                                                                                                                                                                                                                                                                                                                                                                                                                                                                                                                                                                                                                         |
|----------------------------|----------------------------------------------------------------------------------------------------------------------------------------------------------------------------------------------------------------------------------------------------------------------------------------------------------------------------------------------------------------------------------------------------------------------------------------------------------------------------------------------------------------------------------------------------------------------------------------------------------------------------------------------------------------------------------------------------------------------------------------------------------------------------------------------------------------------------------------------------------------------------------------------------------------------------------------------------------|

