| Secondary Outcome Measures | 
 
1. Number of patients without correct diagnostic and management decisions at specified points per 100 patients with measured elevated BP 
 
a. Re-measuring BP twice in clinic via auscultation
 
b. Weight and nutrition counseling
 
c. Repeat BP measurement visits appropriately timed
 
d. Initial laboratory workup
 
e. Subspecialist referral
 
f. Definitive medication management initiation
 
 
 
2. Mean time from first elevated BP to specific points in diagnostic and management process (see #1 above)
 
3. Number of BPs measured correctly with appropriately screened patient, patient position, cuff size, inflation, BP percentiles correctly documented and interpreted per 100 observations conducted
 
4. Time to 3rd next available subspecialist appointment
 
 |

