#### Inclusion Criteria for Initial Visit:

- A patient age  $\geq 3$  years old and  $\leq 21$  years old
- Blood pressure (BP) is elevated  $\geq 90^{\text{th}}$  percentile for patient's height, weight and sex, or  $\geq 120/80$  (regardless of height/sex/weight) at a healthcare maintenance visit or non-acute care visit (e.g. chronic disease follow-up visit). NOTE: This elevated BP measurement can result from oscillometry or auscultation; and it meets inclusion criteria even if a repeated measurement at that visit is normal.

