#### D. Second Elevated BP

If this is the initial visit which qualifies a patient for BP-CATCH, this must be a healthcare maintenance or non-acute care visit. If this patient previously had a qualifying BP-CATCH elevated BP visit above, then this can be any visit when the patient returned for BP follow-up.

1. Date of visit with second elevated BP noted (MM/DD/YYYY): \_\_/\_\_/\_\_\_\_ [THESE DATA ARE ENTERED INTO REDCAP BUT NOT GIVEN TO RESEARCH TEAM]

1a. Height at this visit with an elevated blood pressure \_\_\_\_\_ (centimeters) ☐ Not done at this visit

1b. Weight at this visit with an elevated blood pressure \_\_\_\_\_ (kilograms) ☐ Not done at this visit

2. Systolic Blood Pressure: \_\_\_\_\_ Systolic Percentile: \_\_\_\_\_ ☐ Percentile unknown

3. Diastolic Blood Pressure: \_\_\_\_\_ Diastolic Percentile: \_\_\_\_\_ ☐ Percentile unknown

4. Blood pressure measured by: ☐ Automated (Oscillometry) [Go to 4a] ☐ Manual (Auscultation) [Go to 4c]

4a. Was this BP repeated by manual (auscultation)? ☐ Yes [Go to 4b] ☐ No [Go to 4a.i.]

4a.i. Was automated BP still elevated ( $\geq$  90th percentile for patient's height, weight and sex, or  $\geq$ 120/80)?

☐ No [STOP COMPLETING FORM]

☐ Yes ( $\geq$  90th percentile for patient's height, weight and sex, or  $\geq$ 120/80) [Go to 5]

4b. What were manual BP results: Systolic Blood Pressure: \_\_\_\_\_

Diastolic Blood Pressure: \_\_\_\_\_

4c. Was BP re-measured again with manual ?

☐ Yes [Go to 4c.i] ☐ No [Go to 4e]

4c.i. If Yes, what were additional results: Systolic Blood Pressure #2: \_\_\_\_\_

Diastolic Blood Pressure #2: \_\_\_\_\_ [Go to 4d]

4d. Was average of 2 manual BPs still elevated ( $\geq$  90th percentile for patient's height, weight and sex, or  $\geq$ 120/80)?

☐ Yes [Go to 5] ☐ No [STOP COMPLETING FORM]

4e. Was first manual BP elevated ( $\geq$  90th percentile for patient's height, weight and sex, or  $\geq$ 120/80)?

☐ Yes [Go to 5] ☐ No [STOP COMPLETING FORM]

5. Did provider document that the following were discussed with patient and/or family:

5a. Weight counseling ☐ Yes ☐ No ☐ N/a patient has normal BMI

5b. Nutrition counseling ☐ Yes ☐ No

5c. Lifestyle modifications ☐ Yes ☐ No

6. Did the patient have BP in Stage II Hypertension range ( $\geq$ 95th+12mm to <95th+30mm; or  $\geq$ 140/90 to <180/120)?

☐ Yes [Go to 6a] ☐ No [Go to 7]

6a. Did the patient have BP in Stage II Hypertension range ( $\geq$ 95th+12mm to <95th+30mm; or  $\geq$ 140/90 to <180/120) at the prior visit?

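### Chart Review Tool v.3, Section C, enters two auscultatory readings taken straight after an automated first reading as no re-measurement, which contradicts Table 2 marker 1a

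*Protocol*

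**What the plan says.** Table 2 in Section 4 of the protocol lists secondary marker 1a as "Re-measuring BP twice in clinic via auscultation". It does not ask for an automated repeat first. The primary outcome in the same table is "Number of patients without all correct diagnostic and management decisions", so one step recorded as not done is enough to make the patient an error.

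The appendix data collection guidance accepts either method for the qualifying reading: "This elevated BP measurement can result from oscillometry or auscultation".

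Chart Review Tool v.3, Section C (first elevated BP), routes item 4 as follows: "Automated (Oscillometry) [Go to 4a] ☐ Manual (Auscultation) [Go to 4d". Item 4a then asks "4a. If Automated: was BP remeasured twice with automated device", and a No goes to 4c. Item 4c asks only about a single automated repeat, and its third answer is "No, BP Not re-measured [Go to 5". The manual items open under a stated condition: "4d. If first Manual was abnormal, or repeat automated BPs still elevated: was BP remeasured twice with manual".

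Sections D and E (second and third elevated BP) put the question directly after an automated reading: "Was this BP repeated by manual (auscultation".

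**The concern.** A clinic that follows an elevated automated reading with two auscultatory readings has done what marker 1a describes. Section C has no answer that says so. The abstractor must either tick an untrue statement or improvise, and there is no field for the two manual values.

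Two things are at stake. First, the chart carries a false failure on a listed step of correct care, and that step feeds an all-or-nothing primary outcome. Second, if the manual readings were normal, the instruction to stop the form (item 4d.ii, or 4e for a single reading) is never reached. The child then goes on to the counselling, extremity and follow-up items 5 to 7, which the form would otherwise not have asked. Section C receives every chart that enters as a first elevation.

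**Working it through.** **Routing.** No figure in the plan needs reproducing here. The check is to follow each possible sequence through item 4 of Section C, taking any automated repeat as still elevated.

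| What the clinic did | Path in Section C | What is recorded |
|---|---|---|
| Automated, no repeat of any kind | 4a No, 4c third answer, item 5 | Not re-measured |
| Automated, then one manual | 4a No, 4c third answer, item 5 | Not re-measured |
| Automated, then two manual, average elevated | 4a No, 4c third answer, item 5 | Not re-measured |
| Automated, then two manual, average normal | 4a No, 4c third answer, item 5 | Not re-measured; 4d.ii stop missed |
| Automated, one automated repeat, two manual | 4a No, 4c elevated, 4d Yes | Two manual values; 4d.ii stop available |
| Automated, two automated repeats, two manual | 4a Yes, 4b Yes, 4d Yes | Two manual values; 4d.ii stop available |
| Manual, then two more manual | 4d Yes | Two manual values; 4d.ii stop available |

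The first four rows give the same entries for item 4. Nothing in those entries separates the third and fourth rows, which meet marker 1a as worded, from the first two, which do not. In Sections D and E, item 4a sends the same sequence to the manual fields.

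**Size.** Inputs from the documents:

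- Usual-care error rate of 73% (Sections 1.3 and 6.3).
- Hypothesised 50% reduction under the first collaborative (Section 2, Hypothesis 1), so 0.73 × 0.5 = 36.5%, a difference of 36.5 points.

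Assumptions not in the documents:

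- A share s of charts goes straight from an automated reading to two manual readings.
- Each such chart is scored as an error.
- These charts otherwise have the same error rate e as the rest.

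The observed error rate in a condition is then s + (1 − s)e, an inflation of s(1 − e). With the same s in both conditions the added s cancels, and the observed difference is (1 − s) × 36.5 points.

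| s | Usual care | First collaborative | Difference (points) |
|---|---|---|---|
| 0 | 73.0% | 36.5% | 36.5 |
| 10% | 0.10 + 0.90 × 0.73 = 75.7% | 0.10 + 0.90 × 0.365 = 42.9% | 32.9 |
| 20% | 0.20 + 0.80 × 0.73 = 78.4% | 0.20 + 0.80 × 0.365 = 49.2% | 29.2 |
| 30% | 0.30 + 0.70 × 0.73 = 81.1% | 0.30 + 0.70 × 0.365 = 55.6% | 25.6 |

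For marker 1a alone, the recorded error rate is the true rate plus s. A true 50%, for example, would be recorded as 60% at s = 10% and 70% at s = 20%.

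**The case against.** **Scoring.** No algorithm for marker 1a is printed, and the decision figure that Table 2 cites is not shown. Section C consistently sets out automated repeats first and manual readings afterwards, so that figure might require the same order. This stands: the routing is certain, the scoring is inferred. Even so, a chart that says not re-measured and has blank manual fields supports no score other than an error.

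**Handling in practice.** Section 5 provides an orientation session, clarifications to all teams and secondary chart reviews. An abstractor may notice the misfit. How such charts were actually coded is unknown, but the printed guidance gives no workaround.

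**A stronger reading.** A reader might infer that the fault falls mainly on collaborative charts and so hides much of the intervention effect. With s = 0 in usual care and 10%, 20% or 30% under the collaborative, the 36.5 points would fall to 30.2, 23.8 and 17.5. The documents do not support that contrast. Both cohorts learn accurate BP measurement in the first six months (Section 3 and Figure 2). The five audited aspects in Section 4 do not include confirmation by auscultation. A difference in s between conditions is possible but not shown.

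**Size.** The 36.5% is only the hypothesised rate, and the inflation s(1 − e) is smaller when e is high. Section 1.2 reports that over 75% of patients did not return on time for later readings. If those charts count as errors (an assumption), e is about 0.75, and the inflation within a condition is 2.5, 5.0 and 7.5 points for s = 10%, 20% and 30%. At e = 0.365 it would be 6.4, 12.7 and 19.1. Even the smallest difference in the equal-share table, 25.6 points, is far above the 3-point step that Section 6.3 claims is detectable. These points stand and limit the severity.

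**Timing.** The collaborative was paused in March 2020, and the home-monitoring phase uses tool v.4, which records two office manual readings directly. Editing v.3 therefore has little prospective value. This also stands, but the collaborative data are still to be analysed and published (Section 3).

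**Conclusion.** The inconsistency is real and can be read off the form. Section C cannot record a sequence that satisfies marker 1a as worded, and it merges that sequence with no re-measurement. Sections D and E do not have the fault.

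That these charts become errors on marker 1a and on the primary outcome is the only reading the recorded data allow, but it remains an inference without the decision figure. The size depends on s, which the documents do not give. If s is the same in every condition and unrelated to the other steps, each risk difference is attenuated by the factor (1 − s), as in the table above. Unequal shares could bias the comparisons in either direction; the documents show neither the direction nor the amount. This is a should-fix point about data capture. It does not say which measurement sequence is clinically right.

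**What to change.** For the November 2018 to March 2020 data:

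1. Count, by study condition, the charts with item 4 = Automated and the third answer at 4c. Their share is an upper bound on s, because it also includes charts that were truly not re-measured and those with a single manual reading. This is one database query.
2. Report marker 1a and the primary outcome twice: as entered, and with marker 1a set aside for the flagged charts. This is one extra analysis run. It does not repair charts that missed a stop instruction.
3. Re-check the flagged visits, or a random sample per condition, from the identifier logs that practices hold. This is the costly part. It falls on up to 64 practices, the flagged set may be large, and Section 3 describes the pressure COVID-19 put on clinics. A sample is a reasonable compromise. It should be done before files are separated from practice identifiers at study end (Section 7.1).

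Wherever v.3 is still in use, reconcile Section C with Table 2 and Sections D and E. Change the third answer of 4c to say that there was no repeat automated reading and send it to 4d. Reword the entry condition of 4d to match, and leave the not-re-measured answer to 4e. Charts with no re-measurement then pass through 4d No and 4e No to item 5 and lose nothing. The cost is a small change to the REDCap branching.

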#### D. Second Elevated BP

If this is the initial visit which qualifies a patient for BP-CATCH, this must be a healthcare maintenance or non-acute care visit. If this patient previously had a qualifying BP-CATCH elevated BP visit above, then this can be any visit when the patient returned for BP follow-up.

1. Date of visit with second elevated BP noted (MM/DD/YYYY): \_\_/\_\_/\_\_\_\_ [THESE DATA ARE ENTERED INTO REDCAP BUT NOT GIVEN TO RESEARCH TEAM]

1a. Height at this visit with an elevated blood pressure \_\_\_\_\_ (centimeters) ☐ Not done at this visit

1b. Weight at this visit with an elevated blood pressure \_\_\_\_\_ (kilograms) ☐ Not done at this visit

2. Systolic Blood Pressure: \_\_\_\_\_ Systolic Percentile: \_\_\_\_\_ ☐ Percentile unknown

3. Diastolic Blood Pressure: \_\_\_\_\_ Diastolic Percentile: \_\_\_\_\_ ☐ Percentile unknown

4. Blood pressure measured by: ☐ Automated (Oscillometry) [Go to 4a] ☐ Manual (Auscultation) [Go to 4c]

4a. Was this BP repeated by manual (auscultation)? ☐ Yes [Go to 4b] ☐ No [Go to 4a.i.]

4a.i. Was automated BP still elevated ( $\geq$  90th percentile for patient's height, weight and sex, or  $\geq$ 120/80)?

☐ No [STOP COMPLETING FORM]

☐ Yes ( $\geq$  90th percentile for patient's height, weight and sex, or  $\geq$ 120/80) [Go to 5]

4b. What were manual BP results: Systolic Blood Pressure: \_\_\_\_\_

Diastolic Blood Pressure: \_\_\_\_\_

4c. Was BP re-measured again with manual ?

☐ Yes [Go to 4c.i] ☐ No [Go to 4e]

4c.i. If Yes, what were additional results: Systolic Blood Pressure #2: \_\_\_\_\_

Diastolic Blood Pressure #2: \_\_\_\_\_ [Go to 4d]

4d. Was average of 2 manual BPs still elevated ( $\geq$  90th percentile for patient's height, weight and sex, or  $\geq$ 120/80)?

☐ Yes [Go to 5] ☐ No [STOP COMPLETING FORM]

4e. Was first manual BP elevated ( $\geq$  90th percentile for patient's height, weight and sex, or  $\geq$ 120/80)?

☐ Yes [Go to 5] ☐ No [STOP COMPLETING FORM]

5. Did provider document that the following were discussed with patient and/or family:

5a. Weight counseling ☐ Yes ☐ No ☐ N/a patient has normal BMI

5b. Nutrition counseling ☐ Yes ☐ No

5c. Lifestyle modifications ☐ Yes ☐ No

6. Did the patient have BP in Stage II Hypertension range ( $\geq$ 95th+12mm to <95th+30mm; or  $\geq$ 140/90 to <180/120)?

☐ Yes [Go to 6a] ☐ No [Go to 7]

6a. Did the patient have BP in Stage II Hypertension range ( $\geq$ 95th+12mm to <95th+30mm; or  $\geq$ 140/90 to <180/120) at the prior visit?

☐ Yes [Go to 6b] ☐ No [Go to 7]

6b. Did the provider document a diagnosis of 'Stage II Hypertension' in notes, billing or problem lists at this visit?

☐ Yes [Go to Section F] ☐ No [Go to Section F]

7. Were both upper extremities and 1 lower extremity blood pressure taken and documented?

☐ Yes [Go to 7a] ☐ No [Go to 8]

7a. If yes, were they abnormal (any leg BP same or lower than arm BP)? ☐ Yes [Go to 7b] ☐ No [Go to 8]

7b. If abnormal, was a referral request to a subspecialist made? ☐ Yes [Go to 7c] ☐ No [Go to 8]

\*Did someone in the clinic tell the patient/family they needed to see a subspecialist and complete referral paperwork?

7c. If a subspecialist referral was made, which specialist? (Check all that apply):

☐ Nephrologist ☐ Cardiologist ☐ Other: \_\_\_\_\_

7d. ☐ N/A: Patient never attended subspecialist visit [Go to 8]

[IF N/A NOT CHECKED] Date first subspecialist visit completed (MM/DD/YYYY): \_\_/\_\_/\_\_\_\_ [THESE DATA ARE ENTERED INTO REDCAP BUT NOT GIVEN TO RESEARCH TEAM]

\*Not date referral request made, but date patient actually saw subspecialist

7e. Date information on the patient was received from subspecialist back to the pediatrician:

(MM/DD/YYYY): \_\_/\_\_/\_\_\_\_ [THESE DATA ARE ENTERED INTO REDCAP BUT NOT GIVEN TO RESEARCH TEAM]

\*If same electronic health record, enter date note was signed by the subspecialist

8. Was a follow-up appointment recommended or made for the patient with the primary care practice?

☐ Yes [Go to 8a] ☐ No [Go to Section E]

8a. If yes, what date was the follow-up appointment scheduled for? (MM/DD/YYYY): \_\_/\_\_/\_\_\_\_ [THESE DATA ARE ENTERED INTO REDCAP BUT NOT GIVEN TO RESEARCH TEAM]

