One of the central challenges to diagnosing pediatric patients with hypertension is the need for three sequential office visits with elevated BP measurements documented to confirm that the BP elevations are sustained. Many patients do not return for second or third BP measurements because they are asymptomatic. In the first year of the BP-CATCH study, we observed this problem first hand as over 75% of patients did not return on time for their second or third BP measurement. This problem is exacerbated by the COVID-19 pandemic and the resulting telemedicine environment, as it becomes even harder for patients to feel safe to return to a clinical site solely for BP measurements.

One potential solution to this problem is confirm the blood pressure elevations in a home environment with home blood pressure monitoring (HBPM). This approach minimizes the need for patients to return for an in-person repeat and confirmatory BP measurement and is family-centered by acknowledging hesitancy to return to clinical environments during COVID-19. HBPM uses an automated BP device to measure resting out of office blood pressure in a standard way. Patients obtain three BP measurements each morning and three each evening for seven days. These measurements are then averaged to help determine if the patient has consistently elevated BPs which would warrant further evaluation and treatment. HBPM is not endorsed as a tool for the diagnosis of hypertension in the current evidenced based guidelines for pediatric hypertension due to insufficient evidence, but it is recommended as an adjunct for out of office management of children with an established diagnosis. Notably HBPM is included in the European pediatric hypertension guidelines as an adjunct for diagnosis, and is a guideline-based tool often used by adult practitioners to aid in the diagnosis and management of adult hypertension.

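### Sections D and E of Chart Review Tool v.3 are labelled for elevated visits but admit normal ones, and no item records return, so a blank section cannot be told from non-return

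*Protocol*

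**What the plan says.** In the Protocol appendix, Section D of the Chart Review Tool (v.3) is titled "D. Second Elevated BP". Item 1 asks for "Date of visit with second elevated BP noted (MM/DD/YYYY", and item 1a is worded "Height at this visit with an elevated blood pressure"; item 1b does the same for weight. Section E carries the same labels for a third elevation.

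The preamble to D is wider. For a child who already has a qualifying visit it says "then this can be any visit when the patient returned for BP follow-up". Item 4 then asks, by route, "Was automated BP still elevated" (4a.i), "Was average of 2 manual BPs still elevated" (4d), or whether the first manual reading was elevated (4e). A No at any of the three ends the form. Section E has the same preamble and the same item 4.

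For primary care follow-up, C7/C7a and D8/D8a record whether an appointment was recommended or made and the date it was scheduled for. Neither records attendance. For subspecialist visits the form does have a box for a child who never attended.

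In Table 2 (Section 4), secondary marker 1c is "Repeat BP measurement visits appropriately timed", secondary outcome 2 is the mean time to each marker, and the primary outcome counts patients without all correct decisions. Section 1.2 reports that "over 75% of patients did not return on time for their second or third BP measurement".

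**The concern.** A chart abstractor gets two instructions. The labels say to open D only for a second elevated reading; the preamble and the stop answers say that a normal follow-up visit may be entered. Section B points towards the labels, because it counts only visits with abnormal and no normal readings when it routes a chart to C, D or E.

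A child who returned on time and was normal may therefore have a dated Section D in one practice and a blank one in another. A child who never returned also has a blank Section D, and no other primary care field separates the two.

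Marker 1c, the time to it and the composite built on it are all exposed. The worked example in Section 4 counts both receiving a repeat measurement and having a further one scheduled, so the scheduled date cannot stand in for receipt. Section 3 says the data from November 2018 to March 2020 will be analysed and published, so the question is still live.

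**Working it through.** The protocol gives no figure for this point, so there is nothing to reproduce. The check is of form logic, followed by an illustration of size.

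**1. Routes through item 4 of Section D (identical in E)**

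| Route | Deciding item | Ways to end |
|---|---|---|
| Automated, no manual repeat | 4a.i | 1 continue, 1 stop |
| Automated, manual repeat, second manual | 4d | 1 continue, 1 stop |
| Automated, manual repeat, no second manual | 4e | 1 continue, 1 stop |
| Manual, second manual | 4d | 1 continue, 1 stop |
| Manual, no second manual | 4e | 1 continue, 1 stop |

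That makes 5 × 2 = 10 routes, of which 5 stop on a normal result. These branches may have been written partly for a qualifying visit whose repeat reading was normal, but nothing restricts them to that. Together with the preamble they admit a normal return.

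**2. What each case leaves on the form**

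Take a chart that entered at Section C and did not stop there.

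- Returned, normal, D opened: date, readings, and a No at 4a.i, 4d or 4e. Identifiable.
- Returned, normal, labels followed literally: D blank.
- Did not return: D blank.

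The last two are identical. C7a holds a scheduled date in either case. D8a is blank whenever D is blank, and is also skipped after a stop.

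D and E each appear once, so the form does not say where an elevated visit goes if D already holds a normal return.

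**3. Illustration of size**

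Inputs:
- Recorded on-time return R = 25%, the complement of the over-75% figure in Section 1.2. It is an assumption that this figure bears on these records; the figure also pools second and third measurements.
- n = share of true on-time returns that were normal and left blank. The documents do not give it.

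True return T = R / (1 − n). Overstatement of non-return = T − R.

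| n | T | Overstatement |
|---|---|---|
| 0% | 0.25/1.00 = 25.0% | 0 points |
| 10% | 0.25/0.90 = 27.8% | 2.8 points |
| 25% | 0.25/0.75 = 33.3% | 8.3 points |
| 50% | 0.25/0.50 = 50.0% | 25.0 points |

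The result is driven almost wholly by n. The table shows sensitivity and is not an estimate.

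**4. Effect on the composite**

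A wrongly blank D changes the primary outcome only on a chart that is otherwise fully correct; a chart failing another marker is an error either way. The effect on the composite therefore cannot exceed the effect on 1c.

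**The case against.** The strongest reply is that the form already provides for normal returns. The preamble admits them, the readings are recorded, and half the routes through item 4 close on a normal result. The data collection guidance also says that subsequent visits are entered longitudinally. The elevated wording may simply be carried over: the HBPM chart tool (v.4) keeps the same height and weight labels for a visit whose reading may be normal. The data section of the protocol promises an orientation session, clarifications to all teams, value checks and secondary chart review by site leads.

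Much of this stands, and it rules out several stronger readings that a reader might infer:

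- *A normal return has no place on the form.* It has one, with date and readings.
- *An entered normal return falsifies the second-elevation date.* It does so only if the date is used without the readings and the No answer beside it, and nothing in the protocol says that it will be.
- *Practices did diverge, or blanks were scored as errors.* The documents do not show how sites completed D, and no scoring rule for a blank is given. Such a rule could properly sit in an analysis plan.
- *The over-75% non-return figure, or the HBPM exclusion of children with a repeat visit, is an artefact of this form.* Section 1.2 does not say how its figure was obtained. The HBPM exclusion does not refer to Section D and is not limited to elevated visits.

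The reply does not remove the contradiction between labels and branches, nor supply a field for return. Training may make blanks rarer, but it cannot make an existing blank readable. An analysis plan cannot recover attendance that was never recorded.

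**Conclusion.** The point holds as a form defect that bears on named outcomes. The labels of D and E contradict their own preamble and stop branches, and return to primary care is nowhere recorded explicitly. A timely normal return may therefore be indistinguishable from non-return, which can misclassify marker 1c, the time to it and, through 1c, the primary composite.

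The size is unknown. It is zero if every practice entered normal returns, about 3 points if 10% of on-time returns were left blank and 25 points if half were, all on an assumed 25% recorded return. The documents favour no value of n. They also give no evidence that the habit differed between study conditions, so no bias in the treatment comparison is claimed. The correction is worth making because it is cheap and the first-year data are still to be reported.

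**What to change.** 1. **Relabel.** In D and E, reword the title and items 1, 1a and 1b as a BP follow-up visit, without presupposing an elevated reading.
2. **Add one item before each section:** Returned for BP follow-up? Yes/No; date; reading normal or elevated. State where a later elevated visit is entered when an earlier return was normal.
3. **Scoring.** Score attendance within 1c on the new item. Define a second or third elevation from the recorded readings, not from the presence of a D1 or E1 date.
4. **Charts already collected.** New fields cannot repair these. Where a chart entered at Section C, did not stop there and has a blank Section D, treat return status as unknown, not as non-return, and query the practice where feasible. Practices were told to keep patient identifiers locally for longitudinal entry, so a query is possible in principle. Do not substitute C7/C7a or D8/D8a: the first pair measures scheduling, and the second is empty when D is blank. Report how many charts remain unknown.

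Steps 1 and 2 still have a use, because the protocol says the pre-COVID outcomes will continue to be tracked in patients contacted for HBPM.

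Cost: a few extra fields, some queries to practices, and a number of charts whose return status stays unknown.
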